### Economic evaluation

The economic evaluation will have a trial-based component and a modelled evaluation of long-term costs and outcomes. The economic evaluation will be conducted from both health system as well as societal perspectives. The study will collect information on health care utilisation and out-of-pocket expenditures incurred during the trial for outpatient visits, inpatient care and medications as well as lost productivity. Intervention costs will be based on salaries, training and equipment related to delivering the intervention. A trial-based incremental cost effectiveness ratio (ICER) will be determined by average differences in the number of remissions between study arms as well as average differences in utility observed between study arms using the EQ. 5D questionnaire [38]. If the intervention shows a significant difference in primary outcomes, a decision-analytic model will enable lifetime cost; long-term morbidity, quality of life and survival; and quality-adjusted life years gained to be simulated. Sensitivity analyses will be conducted to determine the robustness of the assumptions used for discount rates, intervention costs, effectiveness and other relevant model parameters used to estimate cost-utility under different scenarios. Cost-effectiveness acceptability curves will be generated to show the probability of cost-effectiveness of the intervention at a range of willingness to pay thresholds. If no significant difference is found for the primary outcomes, a cost-minimisation analysis will be performed. This comprehensive, multi-perspective economic evaluation will better inform policy makers of the resource consequences and associated benefits of implementing this programme to scale.

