### Primary outcomes

There are two primary outcomes corresponding to the study hypothesis.
The mean difference in PHQ-9 scores at 12 months will be assessed in the high-risk cohort.The difference in mean behaviour scores at 12 months using the Mental Health Knowledge, Attitude and Behaviour (KAB) scale will be analysed in the combined high-risk and non-high-risk cohort.

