### Statistical considerations

Assuming a prevalence of 4% of adults with or at high risk of CMDs, we anticipate that around 165,000 adults in total (i.e. 3750 per PHC) will need to be screened at baseline to achieve the required sample size.

In the high-risk cohort, sample sizes of 1936 in intervention and 1936 in control (total 3872), obtained by sampling 22 clusters with an average of 88 subjects each in intervention group and 22 clusters with an average of 88 subjects each in control group at the end of trial, will provide 90% power to detect a standardised mean difference of 0.4 in PHQ-9. The sample size is based on pilot study estimates [5, 37] and ICC. The sample size is based on the primary outcome. These calculations assume an intra-class correlation coefficient (ICC) of 0.15, a coefficient of variation of cluster sizes of 0.65 and a two-sided significance level of 0.05. Power Analysis and Sample Size System (PASS) software licensed by NCSS has been used for sample size estimation.

In the non-high-risk cohort, although the primary outcome will be reported for the combined high-risk and non-high-risk cohort, the study is powered on each sub-group. Sample sizes of 1936 in intervention and 1936 in control (total 3872), obtained by sampling 22 clusters with an average of 88 subjects each in intervention group and 22 clusters with an average of 88 subjects each in control group at the end of trial, will provide > 90% power to detect a standardised mean difference of 0.3 in mean behaviour scores between the intervention and control arms in each cohort. Assuming a mean behaviour score of 2 (SD 1) at baseline, and a 20% relative improvement in the control group (score of 1.6) by 12 months based on pilot and published data [37], this corresponds to a 35% improvement in the intervention group (score of 1.3) and a between-group difference of 0.3 points. This assumes a conservative ICC of 0.05 (0.01 in pilot and 0.04 in similar studies) [37], and a 2-sided significance level of 0.05.

To allow for 20% loss to follow-up during the intervention, at least 110 individuals per PHC in the high-risk cohort and at least 110 individuals per PHC in the non-high-risk cohort will be recruited.

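### Cost-minimisation is triggered by non-significant primary outcomes, which in this superiority trial do not show equal effects on the economic outcome measures

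*Protocol article*

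**What the plan says.** The Economic evaluation section contains three statements that bear on this point.

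- The within-trial analysis carries no condition: "A trial-based incremental cost effectiveness ratio (ICER) will be determined by average differences in the number of remissions between study arms", and likewise by the between-arm difference in EQ-5D utility.
- The long-term model depends on a significance test: "If the intervention shows a significant difference in primary outcomes, a decision-analytic model will enable lifetime cost" and the other long-term outcomes to be simulated.
- A null result leads to a different analysis: "If no significant difference is found for the primary outcomes, a cost-minimisation analysis will be performed".

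Acceptability curves are also planned. They follow the sentences on the model, and the text does not say whether they apply to the within-trial analysis as well.

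The trigger refers to the primary outcomes, and under Primary outcomes the article says: "There are two primary outcomes corresponding to the study hypothesis". These are PHQ-9 in the high-risk cohort and the KAB behaviour score in the combined cohort. Under Statistical considerations both are powered to detect a difference. No equivalence margin or equivalence test between arms appears anywhere. The one use of the word equivalence, under Study design, concerns the high-risk and non-high-risk cohorts, not the arms.

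**The concern.** Cost-minimisation sets the effect difference to zero. A superiority test that fails to reach significance does not justify that, because it only means that the confidence interval includes zero. Whether the interval also excludes worthwhile benefit depends on its width, and the rule does not look at the width.

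The trigger is also on the wrong variables. Even firm evidence that the arms have the same PHQ-9 and behaviour scores would not establish equality on remission or EQ-5D utility, which are the effects in the economic analysis.

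Cost-effectiveness is a stated study objective and the results are meant for policy makers. After a null primary result they would be given a costs-only comparison that rests on an equality the trial did not demonstrate.

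**Working it through.** **Inputs** (Statistical considerations). PHQ-9: "obtained by sampling 22 clusters with an average of 88 subjects each in intervention group", and the same in control, so 22 × 88 = 1936 per arm; "an intra-class correlation coefficient (ICC) of 0.15, a coefficient of variation of cluster sizes of 0.65 and a two-sided significance level of 0.05". Stated result: "will provide 90% power to detect a standardised mean difference of 0.4 in PHQ-9". Behaviour score: same numbers, ICC 0.05, "> 90% power to detect a standardised mean difference of 0.3 in mean behaviour scores".

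**1. Reproduce the plan's PHQ-9 power.**
- Design effect with equal clusters: 1 + (88 − 1) × 0.15 = 14.05.
- Relative-efficiency correction for unequal clusters: λ = 88 × 0.15 / 14.05 = 0.9395, and 14.05 / [1 − 0.65² × 0.9395 × 0.0605] = 14.40.
- Effective n per arm: 1936 / 14.40 ≈ 134.5.
- SE of the standardised mean difference: √(2 / 134.5) = 0.122.
- Power at 0.4: Φ(0.4 / 0.122 − 1.96) = 0.907, or 0.893 with t on 42 df. The stated 90% reproduces. The more conservative correction, 1 + [(0.65² + 1) × 88 − 1] × 0.15 = 19.63, gives 0.80 and does not, so the smaller SE is used below.

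**2. What a non-significant PHQ-9 result can still contain.**
- 95% half-width: 1.96 × 0.122 = 0.239 (0.246 with t).
- Largest non-significant estimate: just under 0.239, with an upper limit just under 2 × 0.239 = 0.478.
- The interval includes 0.4 for every non-significant estimate above 0.4 − 0.239 = 0.161.

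**3. How often PHQ-9 alone is non-significant when an effect exists.** About 63% at a true difference of 0.2, 31% at 0.3 and 9% at 0.4. The 0.2 and 0.3 are assumed values; 0.4 is the plan's.

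**4. What equivalence would require.** With two one-sided 5% tests and a true difference of zero, power is 2Φ[(margin − 1.645 × 0.122) / 0.122] − 1, or zero if this is negative. The document gives no margin, so a range is shown.

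| Assumed margin (SD) | Power to show equivalence |
|---|---|
| 0.2 | about 0% |
| 0.3 | about 59% |
| 0.4 | about 90% |

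**5. Behaviour score.** Without a cluster-size correction the design effect is 1 + 87 × 0.05 = 5.35, the SE √(2 × 5.35 / 1936) = 0.074 and the half-width 0.146. A non-significant estimate has an upper limit below 2 × 0.146 = 0.29, just under the design effect of 0.3. This outcome is more precise, but an upper limit of up to 0.29 is still not equality.

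**The case against.** Several points on the other side stand.

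- **The ICER is not withdrawn.** A reader might infer that the plan switches to costs only and discards the effect estimate. The text does not say so. The trial-based ICER is unconditional, and Statistical considerations reports the intervention effect with its 95% interval whatever the p-value. Cost-minimisation may be an addition. Even then, it is an equal-effects analysis without support.
- **The intervention need not lose on cost.** A reader might infer that a costs-only comparison goes against the intervention by construction. It does so only if net cost is higher. The plan counts outpatient and inpatient care, medication, out-of-pocket spending and lost productivity, so offsets are possible.
- **The PHQ-9 percentages are not the trigger rate.** If both primaries must be non-significant, the rule fires no more often than the rarer of the two events. The behaviour score is non-significant about 2% to 3% of the time at its design effect of 0.3 (single-cohort inputs, with no or relative-efficiency cluster-size correction), and about 23% to 28% at an assumed 0.2. At the planned effects the rule would seldom apply.
- **Baseline adjustment is ignored in the SE.** The planned model includes baseline PHQ-9, which would normally narrow the interval. No correlation is given. To bring 2 × half-width below 0.4, the variance would have to fall by 1 − (0.2 / 0.239)² = 30%, and a limit of nearly 0.4 would still not be equality.
- **Gating the lifetime model is defensible.** Extrapolating only after a positive trial is a reasonable choice about resources and credibility, and is not treated here as an error.
- **One significant primary, one not.** A condensed article could leave this case to a fuller plan. It is an ambiguity to clear up while the sentence is being changed, not a separate fault.

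**Conclusion.** The concern holds as a fault in a stated decision rule. Non-significance on PHQ-9 and behaviour does not establish equal remission or equal utility. On PHQ-9 it does not even exclude the effect that the trial was designed to find: the upper limit can approach 0.48 against a design effect of 0.4. This rests on the plan's ICC, cluster numbers and coefficient of variation, with the SE that reproduces its stated power and no baseline adjustment.

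The documents do not support a claim that effect estimates would be suppressed, that the intervention must appear dearer, or that the rule would fire about half the time. Whether cost-minimisation replaces or supplements the ICER is unstated, and the rule needs correcting on either reading.

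This should be fixed, but it does not threaten the trial. The sample size, randomisation and primary clinical analyses are unaffected.

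**What to change.** 1. Delete the cost-minimisation sentence. If the sponsor wishes to keep it, make it conditional on equivalence shown on the economic effect measures (remission and EQ-5D utility) against a margin fixed before unblinding.
2. State that the trial-based cost-effectiveness and cost-utility analyses are reported whatever the primary p-values, with joint uncertainty in incremental cost and effect that respects PHC clustering (for example a cluster-level bootstrap or a bivariate model), and that the planned acceptability curves apply to them.
3. Whether to run the lifetime model after a null result may stay the sponsor's choice. If the gate is kept, say which branch applies when only one primary is significant.

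The cost is a small change of text and a little more analysis if the result is null. No new data are needed.

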### Process evaluation

Normalisation process theory (NPT) [39], behaviour change theory [40] and MRC Framework for evaluating complex interventions [41] will inform the process evaluation. This will help identify local contextual factors that promote and inhibit the incorporation of a complex intervention into routine practice. This is a critical aspect of the project as it will build on the trial findings to assess scalability of the model. A case study approach will be taken, in which a purposive sample of PHC clusters will be selected to maximise variation in characteristics such as size, urban/rural, health service and baseline performance for the primary outcome. Based on prior studies, we expect around 8 PHC cases (with 24 villages) will provide enough breadth to capture a diversity of experiences with the intervention whilst allowing us to acquire a deep understanding of implementation processes within each case. A mixed methods approach will be employed to understand effective intervention strategies and significant intervention components that go into the SMART Mental Health programme. Four data sources will be used: site-specific analyses of trial data; usage analytics of the applications; quantitative satisfaction and feasibility surveys using the standardised system usability scale [42]; and in-depth, semi-structured interviews with doctors, ASHAs and community members toward the end of the study. Survey and interview instruments will be iteratively developed, guided by our overarching theories, and tested prior to implementation.

### Ethical considerations

The study is approved by the George Institute for Global Health India and All India Institute of Medical Sciences (AIIMS), New Delhi Institutional Ethics Committee (IEC). The Clinical Trial Registry of India number (CTRI/2018/08/015355) has been obtained from the National Institute of Medical Statistics, Indian Council of Medical Research (ICMR). The trial was registered on 16 August, 2018, but no patients have been recruited yet in the trial (due to the COVID crisis recruitment has been postponed to later this year) (http://ctri.nic.in/Clinicaltrials/showallp.php?mid1=23254&EncHid=&userName=CTRI/2018/08/015355). Approval of the SMART Mental Health programme from the Health Ministry’s Screening Committee (HMSC), ICMR has also been received. Letters of support from the Director General of Health Services (DGHS) of Andhra Pradesh and Haryana state governments as well as permission letters from Chief Medical Officers/Civil Surgeons at the district health department level have been granted. Preliminary discussions about the study and interventions with each village Panchayat, PHC doctors and ASHAs were conducted during the initial village mapping and household listing exercises. Informed consent will be obtained from all participants by ASHAs at the time of screening for high-risk populations and by the trained interviewers prior to administering the detailed questionnaire at baseline. Any individual identified at imminent risk of suicide at baseline will be advised to seek professional help from a doctor/psychiatrist immediately whose contact details would be provided. All data collection and reporting will be compliant with national privacy laws. Independent study monitoring will occur for a subset of participants. Data will be de-identified, stored on George Institute India servers, and held in strict compliance with Good Clinical Practice guidelines using our standard operating procedures for data security, confidentiality, backup, and audit trails. As required, all raw data and any derived datasets will be preserved for at least 10 years from study completion. Any data required to support the protocol can be supplied on request and the datasets analysed during the current study are available from the corresponding author on reasonable request. This trial does not involve collecting biological specimens for storage.

### Adverse event reporting

Serious adverse events will be captured after the start of the intervention phase. This will be defined as death due to any cause in the intervention or control arm, hospitalisation due to psychiatric disorders or a history of self-harm or attempted suicide during the intervention period. These events will be captured using a standardised case report form and reported to an independent Data Safety Monitoring Committee and Ethics Committee at interim analysis and at end of study.

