### mHealth-based EDSS

Separate EDSS modules were developed for ASHAs and PHC doctors. The software was developed on an Android platform, optimised for 7-in. tablets. The EDSS for ASHAs included a screening tool based on the Patient Health Questionnaire (PHQ-9) [28, 29] and Generalised Anxiety Disorders (GAD-7) instruments [29, 30]. Both these scales have been validated in India [31]. The diagnostic and management guidelines used by the PHC doctor are based on WHO’s Mental Health Gap Action Programme-Intervention Guide (mhGAP-IG) [32] and focus on three conditions: depression, anxiety and self-harm/suicide. The mhGAP-IG is in English. The algorithm has been modified based on multiple iterations and feedback from the research team and a psychiatrist and has been validated in a previous mixed methods study [26]. The treatment algorithm provides guidelines about both pharmacological and psychological treatment including referral. A traffic-light dashboard was also developed to support ASHAs to follow-up screen-positive individuals and act on the treatment provided by the doctors.

The implementation of the enhanced mobile technology-based EDSS for ASHA and PHC doctors to identify and treat people at high risk of CMDs includes the following:

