Non-physician health workers (ASHAs) are trained to use the PHQ-9 and GAD-7 to screen adults (≥ 18 years) in the village for CMDs. They use a tablet-based questionnaire to generate composite scores to identify ‘high-risk’ individuals.ASHAs can then provide basic supportive advice and a referral to the PHC doctor. Participants are electronically referred via the mHealth platform and provided with a paper referral card to take to the doctor.The PHC doctor then reviews participants as part of a village health camp visit or the patient can directly visit the PHC. Data from individuals are uploaded, with consent, to a secure health record using the OpenMRS open source, electronic health record system.A decision support application based on WHO’s mhGAP-IG algorithm is integrated in a tablet device and used by PHC doctors to diagnose and manage patients experiencing CMDs. Doctors can use the depression, self-harm/suicide and emotional or medically unexplained complaints’ modules of mhGAP-IG. Patients requiring medication can access these directly from the PHC or purchase low-cost generics from a private pharmacy.For people with complex needs, consultation with a specialist psychiatrist is available as needed. The psychiatrist can also conduct case reviews via phone and/or video conferencing with the PHC doctors to enhance their management skills. Alternatively, people can be referred by the PHC doctor to a psychiatrist in the next tier of the public health system.Mobile-based messages are sent to ASHAs to ensure adherence and follow-up of those individuals who are diagnosed with CMDs by PHC doctors. ASHAs are able to conduct follow-up visits and assess treatment adherence using a recall and reminder (priority listing) system installed on their mobile devices. ANMs will also assist in streamlining the referral system by ensuring that patients under treatment are regularly followed-up.An algorithm-based interactive voice response system is able to send out pre-recorded messages to diagnosed patients to continue care as advised by the PHC doctor and ASHA, and similar motivational messages can be sent to ASHAs to screen and follow up patients as per guidelines.

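### The serious adverse event definition counts only psychiatric hospitalisation, so non-fatal medical admissions, including those from medicine harm, do not reach the safety committee

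*Protocol article*

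**What the plan says.** The Adverse event reporting section gives a definition, not examples. Its components are "death due to any cause in the intervention or control arm" and "hospitalisation due to psychiatric disorders or a history of self-harm or attempted suicide during the intervention period". Deaths count whatever the cause, but hospitalisations count only if psychiatric. I read self-harm and attempted suicide as events in their own right; if they were meant only as reasons for admission, an admitted case would still count. No category for medicine-related harm is given. The listed events are to be "reported to an independent Data Safety Monitoring Committee and Ethics Committee at interim analysis and at end of study".

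The mHealth-based EDSS section describes what the intervention arm adds. On the doctors' tool it says: "The treatment algorithm provides guidelines about both pharmacological and psychological treatment including referral". On supply it says: "Patients requiring medication can access these directly from the PHC or purchase low-cost generics from a private pharmacy". Community health workers follow up adherence with reminders, a specialist can be consulted, and "people can be referred by the PHC doctor to a psychiatrist in the next tier of the public health system".

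The Economic evaluation section says: "The study will collect information on health care utilisation and out-of-pocket expenditures incurred during the trial for outpatient visits, inpatient care and medications". These data are described for costing. The article does not say that they feed safety reporting.

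**The concern.** The definition fits this intervention poorly in two ways.

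- **What is left out.** If decision support leads to more prescribing, the most direct physical harm to watch for is a medicine reaction, an interaction or an accidental overdose. When such an event leads to a medical admission and the patient survives, it is not a serious adverse event under the article's definition.
- **What is counted.** Psychiatric admission lies on the intervention's own care pathway. Closer follow-up and referral may change its frequency without any change in how ill people are. A difference between arms in this count would be hard to read, and there is no all-cause admission count to set beside it.

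At stake is whether the committees see the admissions that matter for a programme in which primary care doctors prescribe with decision support, and which the article hopes to see scaled up.

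**Working it through.** **1. Which events are captured**

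| Event in a participant | Reportable under the definition? |
|---|---|
| Death from medicine harm | Yes, as death from any cause |
| Deliberate overdose | Yes, as self-harm or attempted suicide |
| Psychiatric deterioration with admission | Yes, as psychiatric hospitalisation |
| Non-fatal medical admission for a medicine reaction, interaction or accidental overdose | No |
| Any other non-fatal, non-psychiatric admission | No |

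The gap is confined to the last two rows.

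**2. What differs between the arms**

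- Detection does not differ for the evaluation cohorts. Screening and rescreening come before randomisation (High-risk cohort section).
- Support for medicine supply does not differ. It is described under Both arms, for all participating PHCs.
- Referral of serious cases is partly shared. High-risk control participants are told of their risk and advised to seek care, and those with psychotic symptoms, elevated self-harm risk or other signs of serious illness are referred to a facility with a psychiatrist (Control arm section).
- What remains specific to the intervention is the treatment algorithm, adherence follow-up, specialist consultation and the added referral route (mHealth-based EDSS section).

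A difference in prescribing and in psychiatric admission is therefore plausible, but its size is not known.

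**3. Illustration of scale**

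The article states no prescribing, admission or adverse event rate, so there is no figure to reproduce. Every rate below is an assumption. The one documented input is the high-risk cohort of at least 110 per PHC with 22 PHCs per arm (Statistical considerations section): 110 × 22 = 2,420 per arm.

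*Uncounted medicine-related admissions.* Excess = 2,420 × (extra share medicated) × (risk of a non-psychiatric medicine-related admission).

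| Extra share medicated | Risk 0.2% | Risk 1% |
|---|---|---|
| 10% | 0.5 | 2.4 |
| 30% | 1.5 | 7.3 |
| 50% | 2.4 | 12.1 |

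*Counted psychiatric admissions.* Events per arm = 2,420 × (share needing admission) × (probability of admission if needed). The need is the same in both arms. The probability of admission is 30% in control and 45% or 60% in intervention.

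| Need | Control, 30% | Intervention, 45% | Intervention, 60% |
|---|---|---|---|
| 0.2% | 1.5 | 2.2 | 2.9 |
| 0.5% | 3.6 | 5.4 | 7.3 |
| 1.0% | 7.3 | 10.9 | 14.5 |

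The apparent risk ratio is 0.45 / 0.30 = 1.5 or 0.60 / 0.30 = 2.0, with no difference in need. These ratios are simply the assumed ratios of access. They show what could happen and are not an estimate. If access does not differ, the ratio is 1.

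**4. Reporting burden of a wider definition**

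(110 + 110) × 44 = 9,680 participants in the two cohorts, half of them not at high risk, followed for 12 months.

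**The case against.** The strongest reply is that a short, targeted list of serious events is a defensible choice in a pragmatic service-delivery trial. The list captures the gravest outcomes: any death, self-harm and psychiatric admission. The article condenses a full protocol, and its standardised case report form is not shown. Reason fields, causality assessment and the handling of non-serious reactions may well be set out there. The article also names no between-arm safety test that the definition could bias.

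Much of this stands. It rules out treating the absence of a reason field as a fault, and it limits how much can be said about a safety comparison. It does not remove the gap, because the article states the definition itself. Followed as written, non-fatal medical admissions are not reported to the committees.

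Four stronger readings are tempting, and the article does not support them:

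- **That the intervention raises psychiatric admissions because it finds more people.** Screening precedes randomisation and is common to both arms.
- **That admissions are classified by people who know the arm.** The article does not say who classifies events, and the Data collection section describes field investigators blinded to allocation.
- **That medicine harm would leave no trace.** Fatal harm, deliberate overdose and psychiatric admissions are counted, and inpatient care is recorded for costing.
- **That 4 to 15 serious events would be missed.** That range comes from assuming that 30% of 2,420 are medicated (726) and that 0.5% to 2% of them are admitted. It is a gross count in one arm. A comparison needs the excess over control, where people may also be treated.

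**Conclusion.** The concern holds in a narrow form. By the article's own definition, non-fatal, non-psychiatric admissions, including those from a medicine reaction, an interaction or an accidental overdose, do not go to the safety and ethics committees, although the intervention adds algorithm-guided drug treatment. This follows from the text and needs no assumed rate.

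The second part is weaker. Psychiatric admission may be affected by the intervention's extra follow-up and referral, but shared screening, referral of serious control cases and medicine supply support in both arms leave the size of any difference unknown.

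Neither effect can be sized from the article. The 0.5 to 12 uncounted excess admissions and the apparent risk ratios of 1.5 to 2.0 rest wholly on assumed rates. This is an inexpensive improvement to safety reporting that should be made. It does not show that the safety data will be misleading.

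**What to change.** In the Adverse event reporting section, extend the reportable events to hospitalisation for any cause, with the reason recorded. If that is judged too broad, add at minimum admissions suspected to be medicine-related.

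Report three counts by arm to the committee: all-cause, psychiatric and suspected medicine-related admissions. Cross-check the event forms against the inpatient and medication data already collected for the economic evaluation, so that admissions missed by one route are found by the other.

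The cost is more event forms to process and tabulate across 9,680 participants at the planned cohort sizes. The change does not fully separate better access from deterioration: a psychiatric admission after referral is still coded as psychiatric whichever caused it. Psychiatric admissions should therefore be interpreted alongside the all-cause count.
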